## Abstract

**Background:**

Lateral hip pain is common, particularly in females aged 40–60 years. The pain can affect sleep and daily activities, and is frequently recalcitrant. The condition is often diagnosed as trochanteric bursitis, however radiological and surgical studies have revealed that the most common pathology is gluteus medius/minimus tendinopathy. Patients are usually offered three treatment options: (a) corticosteroid injection (CSI), (b) physiotherapy, or (c) reassurance and observation. Research on Achilles and patellar tendons has shown that load modification and exercise appears to be more effective than other treatments for managing tendinopathy, however, it is unclear whether a CSI, or a load modification and exercise-based physiotherapy approach is more effective in gluteal tendinopathy. This randomised controlled trial aims to compare the efficacy on pain and function of a load modification and exercise-based programme with a CSI and a ‘wait and see’ approach for gluteal tendinopathy.

**Methods:**

Two hundred one people with gluteal tendinopathy will be randomly allocated into one of three groups: (i) CSI; (ii) physiotherapist-administered load modification and exercise intervention; and (iii) wait and see approach. The CSI therapy will consist of one ultrasound (US) guided CSI around the affected tendons and advice on tendon care. Education about load modification will be delivered in physiotherapy clinics and the exercise programme will be both home-based and supervised. The group allocated the wait and see approach will receive basic tendon care advice and reassurance in a single session by a trial physiotherapist. Outcomes will be evaluated at baseline, 4, 8, 12, 26 and 52 weeks using validated global rating of change, pain and physical function scales, psychological measures, quality of life and physical activity levels. Hip abductor muscle strength will be measured at baseline and 8 weeks. Economic evaluation will be performed to investigate the cost-effectiveness of the active interventions compared with the wait and see approach. Analyses will be conducted on an intention-to-treat basis using logistic and linear mixed regression models and the economic evaluation will report incremental cost-utility ratios. The trial reporting will comply with CONSORT guidelines.

**Discussion:**

This study will provide clinicians with directly applicable evidence of the relative efficacy of three common approaches to the management of gluteal tendinopathy.

**Trial registration:**

Australia New Zealand Clinical Trials Registry ACTRN12612001126808. Date Registered: 22/10/2012.

**Electronic supplementary material:**

The online version of this article (doi:10.1186/s12891-016-1043-6) contains supplementary material, which is available to authorized users.

## Background

Gluteal tendinopathy or greater trochanteric pain syndrome is a debilitating condition, characterised by pain situated at or around the greater trochanter of the hip, and tenderness on palpation. Although traditionally considered to be trochanteric bursitis, more advanced imaging and surgical procedures in people with lateral hip pain have revealed a primary pathology of insertional gluteus medius or minimus tendinopathy, with bursal distention generally a concomitant finding [1–3]. Magnetic Resonance Imaging (MRI) is very effective in recognizing partial and full thickness tears of the tendons of gluteus medius and minimus, tendon calcification and fatty muscle atrophy [2]. For the purposes of this paper we will refer to the condition of gluteus medius tendinopathy, and/or gluteus minimus tendinopathy, with or without bursal distention, as gluteal tendinopathy.

The condition is more frequent in women aged 40–60 years [4], and various studies have described its prevalence as ranging from 10 to 25 % of the general population [5, 6]. A recent study of general medical practice in the Netherlands found gluteal tendinopathy to have the highest prevalence (4.22 per 1000 person years) and incidence (3.29 per 1000 person years) of all presenting lower limb tendinopathies [7]. The impact of gluteal tendinopathy can be substantial. The pain experienced in side lying often creates significant sleep disturbance, and the pain commonly experienced with walking and stair climbing usually results in reduction of physical activity levels, which could be expected to have negative implications for general health and well-being, as well as quality of life and employment status [8].

It is proposed that abnormal hip biomechanics may predispose to gluteal tendinopathy [9], and although commonly diagnosed in sedentary, overweight people [5], it is also often seen in runners, possibly due to both poor training habits and technique [10]. It has been hypothesised that gluteal tendinopathy, with or without bursitis, occurs due to compressive impingement of these structures onto the underlying greater trochanter by the iliotibial band (ITB) as the hip moves into adduction [11, 12]. In an upright weight bearing posture, such as walking, weakness of the hip abductor muscles will result in lateral pelvic tilt or ipsilateral shift in single leg stance, and hip adduction, which will contribute to compression of the tendons between the greater trochanter and the thick fascia of the ITB.

The literature reflects an assumption that tight lateral structures are a key issue for the development of gluteal tendinopathy. Despite a lack of evidence of such tightness, the conservative management approach commonly suggested is stretching [13]. Compression as a primary aetiological factor is consistent with current theories for development of insertional tendinopathy [14, 15], and failure to control compression in a treatment protocol for insertional Achilles tendinopathy has been reported to result in poor outcomes [16]. The piriformis and iliotibial band stretches frequently prescribed [13] involve sustaining the hip in forced adduction, which is a position of high compressive loads on the gluteal tendons [17]. We hypothesise that a specific focus on hip abductor muscle function and avoidance of compressive loads on the tendons will provide a better approach to achieve effective treatment outcomes.

A range of conservative management approaches are generally recommended, including anti-inflammatory medications, rest, ice, heat, stretching, strengthening, ultrasound, shock-wave therapy (SWT), and local corticosteroid injection (CSI). Surgery is usually reserved for when the condition has become refractory and conservative measures have failed. However, optimal management of gluteal tendinopathy remains unclear. Reports concerning management of this condition predominantly relate to CSI and surgery. Early response to CSI in patients with lateral hip pain is reported to be very good, with 70–75 % of patients reporting a significant improvement at 1 month post injection in a randomised clinical trial (RCT) [13, 18]. However, at 3–4 months post injection, researchers have reported only 41–55 % positive response [13, 19]. At 12 months an RCT showed no difference between a CSI and a group that adopted a wait and see policy [19]. In the only clinical trial (non-randomised) to date to compare CSI to home exercise, the success rates at 1 month were 75 and 7 % respectively, but by 15 months were 48 % for CSI and 80 % for the home exercise group [13], demonstrating only short term benefits of CSI. These studies of CSI highlight the typical trajectory of delayed healing after a short term improvement, which in some studies is also coupled with substantial recurrence rates [20].

Most patients and their medical practitioners understandably seek a positive early response. Although Rompe et al report patient satisfaction with a slow rate of improvement in the early stages, a 7 % success rate for home exercise after 1 month [13] is not convincing evidence to recommend exercise to a patient who would otherwise have a 75 % chance of a successful early outcome with CSI. In contrast, outcomes from exercise and manual therapy for a comparable tendinopathy at the elbow (tennis elbow or lateral elbow tendinopathy, with similar age demographic) are comparable to those from CSI at 6 weeks (65 and 78 % success rates respectively) and superior to adopting a wait and see approach [21]. We speculate that the low success rates at 1 month reported by Rompe et al., in contrast to the high early success rates reported by Bissett et al., is the non-specific nature of the prescribed exercises (i.e. not targeting the muscles specifically affected by tendinopathy, using stretches that increase compression), a lack of specific load modification and management strategies related to tendon healing, and a low level of supervision of the home-based exercise programme.

The contemporary non-operative approach to effectively managing tendinopathy involves specific exercise for the affected muscles and load management in the form of advice and practical strategies [15]. This approach has yet to be rigorously tested in an RCT. We propose to test different conservative management options for gluteal tendinopathy by comparing an exercise and load management approach supervised by physiotherapists, CSI and the adoption of a wait and see approach.

Our primary hypotheses are that:HI: Both the exercise and load management programme and the CSI will be superior to a wait and see approach in terms of treatment success rates based on global rating of change and reductions in pain at 8 weeks.H2: The exercise and load management programme will be superior to CSI in terms of treatment success rates and reductions in pain at 52 weeks.

The secondary objectives are to: compare an exercise and load management programme with CSI on outcomes including pain, function, hip abductor muscle strength, psychological measures, quality of life and physical activity levels; evaluate the effects of the two treatments compared to a wait and see approach on these outcomes; determine the cost-effectiveness of the two treatments at 52 weeks; compare the adverse events associated with both treatments.

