**Fig. 2 Fig2:**
[figure not shown]
Spring resisted abduction on a sliding platform

Adherence to the exercise programme will be monitored by the physiotherapists and with the participants also completing a daily diary, outlining the exercises completed (number of sets and repetitions), any adverse responses and action taken. If any adverse event occurs during the treatment period, the participants will also be encouraged to report directly to their physiotherapist (e.g. worsening of pain, new symptoms or any injury). Any reports of adverse events will be recorded in the treatment notes and diary. The diary will be collected from the participant at the 8 week follow up assessment.

*Wait and see:* Participants allocated to adopt a wait and see approach will attend one session with a trial physiotherapist, where they will receive reassurance that the condition is likely to resolve over time, as well as advice regarding general tendon care and self-management. They will also receive a standard information pamphlet about the condition and basic self-management. The therapists will take time to answer any questions about adopting a wait and see approach to ensure the participant is confident that this is an appropriate and sensible approach to adopt. Participants in this group will complete a weekly diary, outlining any problems that may have been encountered related to the study.

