### Other measures

Several other measures will be included to provide additional information about participants, such as demographic information collected at phone interview and the initial physical screen. Participants in the CSI and wait and see groups will keep a weekly diary throughout the initial 8 weeks to record any adverse events and any co-interventions, including pain related medication use. This same information is captured via the daily diary in the physiotherapy group.

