### Adverse events

Participants, physiotherapists and medical practitioners performing the treatments will report adverse effects to the research assistant who with the chief investigator will then ensure that if required the appropriate treatment for that adverse effect is undertaken and that the event is reported to the ethics committee. The participant will be monitored over the course of resolution.

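### The adverse-event objective names only the two active treatments; the wait-and-see group, which keeps an adverse-event diary over the same 8 weeks, should be brought into the stated comparison

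*Protocol article*

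**What the plan says.** All references are to the Protocol article.

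- **Background, secondary objectives.** Exercise is compared with CSI on pain, function, strength, psychological measures, quality of life and activity. The plan will then "evaluate the effects of the two treatments compared to a wait and see approach on these outcomes". Adverse events are not in that list. They have their own clause: "compare the adverse events associated with both treatments".
- **Other measures.** "Participants in the CSI and wait and see groups will keep a weekly diary throughout the initial 8 weeks to record any adverse events", together with co-interventions. For exercise, "This same information is captured via the daily diary in the physiotherapy group".
- **Interventions, exercise group (adherence paragraph).** Events to be reported to the physiotherapist are illustrated by "worsening of pain, new symptoms or any injury".
- **Interventions, wait and see.** The same weekly diary is described more narrowly, as "outlining any problems that may have been encountered related to the study".
- **Adverse events.** "Participants, physiotherapists and medical practitioners performing the treatments will report adverse effects to the research assistant". No group is excluded.
- **Statistical analysis.** All three pairwise contrasts are fixed in advance, but as contrasts of treatment means for the scheduled outcomes. Adverse events are not mentioned there.

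**The concern.** For efficacy, the article compares the active treatments with each other and each of them with wait and see. For harm it states only the first kind of comparison. The kinds of event it gives as examples overlap with the course of the condition: a painful hip can become more painful, and new symptoms or an injury can arise, without any treatment. A count of such events in two treated groups mixes the background rate with any effect of treatment.

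If the report follows the objective literally, a reader learns which active treatment had more events, but not whether either had more, or fewer, than participants who were only advised and reassured. A background rate common to both groups could be taken for harm of both treatments. The group that would settle this is randomised, and its diary is already planned.

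**Working it through.** **1. What the stated contrast estimates.** The article gives no adverse-event figure to reproduce, so the first step is logical. Let b be the 8-week risk of an event without active treatment, and h1 and h2 the excess risks under CSI and exercise.

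- CSI minus exercise: (b + h1) − (b + h2) = h1 − h2. The background cancels, and h1 and h2 are not separately estimable.
- CSI minus wait and see: (b + h1) − b = h1.
- Exercise minus wait and see: (b + h2) − b = h2.

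Only the last two answer whether a treatment adds events, and both need the wait-and-see group.

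**2. Whether another section supplies the missing comparison.** The cost-effectiveness clause in the same sentence also names only the two treatments. There the Abstract (Methods) and Statistical analysis make clear that wait and see is the comparator. No section does this for adverse events: the Adverse events section deals with reporting and management, and the three fixed contrasts concern outcome means.

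**3. Whether the efficacy analyses fill the gap.** Average pain is contrasted with wait and see as a mean. Data management dichotomises the global rating of change at moderately better or above, so slightly better, unchanged and every grade of worse fall together as non-success. Neither analysis gives the proportion who worsened, and neither covers new symptoms or injury.

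**4. Whether recording is comparable.**

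| Group | Diary | Planned treatment contact in 8 weeks |
|---|---|---|
| CSI | weekly | one injection visit |
| Wait and see | weekly | one physiotherapist session |
| Exercise | daily | 2 × 1 + 6 × 2 = 14 physiotherapist sessions |

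CSI and wait and see are the most alike. Exercise has more occasions on which an event can be noted.

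**5. Precision.** Sample size gives 67 per group with 15 % loss: 67 × 0.85 = 56.95, about 57 evaluable. With the same event rate p in both groups, the 95 % half-width is 1.96 × √(2p(1 − p)/n). The values of p are assumed.

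| p | n = 67 | n = 57 |
|---|---|---|
| 0.20 | 0.135 | 0.147 |
| 0.30 | 0.155 | 0.168 |
| 0.40 | 0.166 | 0.180 |

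**6. Power, for scale.** Take an assumed wait-and-see risk p1 of 10 % or 20 % and a true excess of 10 points, so p2 = p1 + 0.10, with p̄ their average. Power of a two-sided 5 % test is Φ{[0.10√n − 1.96√(2p̄(1 − p̄))] / √(p1(1 − p1) + p2(1 − p2))}.

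- n = 67: 0.366 (p1 = 10 %) and 0.265 (p1 = 20 %).
- n = 57: 0.319 and 0.232.

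A moderate excess would often go undetected by a test, so these contrasts should be reported as estimates with intervals.

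**The case against.** The strongest reply is that the clause is shorthand. The neighbouring cost-effectiveness clause also omits wait and see, yet wait and see is plainly its comparator, so silence need not mean exclusion. The clause does not say that the treatments are compared only with each other. The layout of a safety table is also something that an article may leave to the full protocol or analysis plan. This has force: nothing bars a three-group table, and one may well be intended. But cost-effectiveness is completed elsewhere in the article and adverse events are not. The point concerns an objective that is stated, and stated more narrowly than the data allow, not a detail left out.

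A reader might go further and infer that background worsening cannot be separated from treatment harm in this trial. The documents do not support that. Wait-and-see events are to be recorded over the same 8 weeks, participants in every group report adverse effects, average pain is formally contrasted with wait and see, and grades of worse on the global rating are collected in all three groups. Nor does the article call the condition fluctuating or give a rate of worsening. It speaks of likely resolution over time and of frequent recalcitrance.

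It is also fair to say that the added contrasts are imprecise and that recording is uneven. Both limit what can be concluded, especially for exercise. Neither is a reason to leave the control group out.

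**Conclusion.** The point holds as a minor gap in a stated comparison. As worded, the objective yields the difference in harm between CSI and exercise, but not the excess of either over no active treatment. The data needed for the second question are already planned.

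The logic in step 1 needs no assumed figure. The half-widths of about 14–17 points (67 per group) or 15–18 points (57 evaluable) rest on assumed event rates of 20–40 %, and the power figures on assumed background risks of 10–20 %. Neither range comes from the article. No sample size or primary analysis is affected. An analysis plan that is not shown may already contain the three-group comparison; if so, only the objective's wording needs to follow it.

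**What to change.** 1. Reword the objective to compare participants with at least one adverse event across all three groups: CSI versus wait and see, exercise versus wait and see, and CSI versus exercise. Give risk differences with 95 % CIs over the common 8-week diary period, presented as estimates rather than tests.
2. Report worsening of hip pain separately from other events, so that symptoms of the condition are not merged with events specific to the injection or the exercises.
3. Bring the wait-and-see diary description under Interventions into line with Other measures, so that this group is asked for any adverse event and not only for problems tied to the study.
4. State when reporting that the daily diary and more frequent physiotherapist contact may raise recorded events in the exercise group, and that CSI versus wait and see has the most similar recording.

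The cost is a line in the objectives, a consistent diary description and an extra column in the safety table, from data already planned. The small downside is wide intervals, which readers must not take as evidence that harms are equal.

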## Methods

This is a pragmatic, assessor-blinded, RCT conducted in medical and physiotherapy clinics in Brisbane and Melbourne, Australia. In people with persistent gluteal tendinopathy, it compares the effect of CSI, a physiotherapy supervised load management, education and exercise programme and a wait and see approach for gluteal tendinopathy over 12 months. The trial protocol will permit its reporting in line with the CONSORT guidelines [22].

### Participants

Lateral hip pain, which is a symptom of gluteal tendinopathy, might also present with other pathologies, such as trochanteric bursitis, osteoarthritis, referred lumbar spine pain, and femoral stress fracture [23]. As the load modification and exercise programme in this trial has been designed specifically to address gluteal tendinopathy, it is important that other differential diagnoses for lateral hip pain are excluded.

#### Recruitment details

We will recruit people from the community in both Brisbane and Melbourne via advertisements in University News, social media and local newspapers. Initial contact will be by phone or electronic media at which time a preliminary screening for suitability will occur. If the phone interview indicates potential eligibility, the volunteer will attend the trial centre for a physical examination, which will assess against specific selection criteria. Those who meet these criteria will then undergo diagnostic imaging to confirm eligibility prior to being included in the trial.

#### Selection criteria

We will include participants between the ages of 35 and 70 years who have experienced lateral hip pain for at least 3 months, of an intensity of ≥4/10 on an 11-point numeric rating scale on most days of the last 3 months. Table 1 outlines the selection criteria for inclusion into the study. These criteria were based on a previous study [13].

**Table 1 Tab1:** Inclusion and Exclusion Criteria

Inclusion criteria
Lateral hip pain, worst over the greater trochanter, present for a minimum of 3 months
Age 35–70 years
Pain at an average intensity of ≥4 out of 10 on most days of the week.
Tenderness on palpation of the greater trochanter
Reproduction of pain on at least one of five diagnostic clinical tests (FABER test, Static muscle contraction in FABER position, FADER test, Adduction test, Static muscle contraction in Adduction position i.e. resisted abduction) or single leg stand
Demonstrated tendon pathology on MRI (see Table 2 for criteria)
Exclusion Criteria
Previous cortisone injection in the region of the lateral hip in the last 12 months
Physiotherapy intervention or regular appropriate Pilates in the last 3 months
Lumbar spine or lower limb surgery in the previous 6 months
Any known advanced hip joint pathology where groin pain is the primary complaint and/or where groin pain is experienced at an average intensity of ≥2 on most days of the week, or Kellgren-Lawrence score of >2 (mild) on XRay.
Where range of pure hip joint flexion is <90°
Significant signs of lumbar pathology
Known advanced knee pathology or restricted range of knee motion (must have minimum 90° flexion and full extension)
Any systemic diseases affecting the muscular or nervous system, and uncontrolled diabetes
Malignant tumour
Systemic inflammatory disease
Any factors that would preclude the participant from having an MRI (e.g. pacemaker, metal implants, pregnancy, claustrophobia)
If the participant is involved in a legal/workcover/TAC or other injury claim
If the participant is unable to commit to an 8 week exercise programme with twice weekly supervised sessions
Fear of needles (trypanophobia)
If the participant is unable to write, read or comprehend English

As clinical tests to diagnose gluteal tendinopathy appear to have limited validity [24], we have included a small battery of clinical tests that have been considered to be most provocative in reproducing symptoms of gluteal tendinopathy [23]. To be eligible, the participant must experience pain on direct palpation of the gluteal tendons’ insertion on the greater trochanter. They must also test positive (reproduction of trochanteric pain) to at least one of the following clinical tests: the Hip FADER (passive) test, static muscle test in the FADER position, the FABER (Patrick’s) test, passive hip adduction in side lying (ADD), a static muscle contraction in the ADD test position, and a Single Leg Stance on the affected leg for 30 s.A.*Hip FADER* – With the patient supine, the hip is passively flexed to 90°, adducted and externally rotated to end of range (FADER = Flexion/Adduction/External Rotation). The pain Numeric Rating Scale (NRS) and area of pain is recorded. This test positions the ITB over the greater trochanter and places the Gluteus Medius (GMed) and Gluteus Minimus (GMin) tendons under tension while being compressed against the greater trochanter by the overlying fascia of the ITB. The test is only recorded as positive if the pain (≥2/10) is experienced over the lateral hip.B.*Hip FADER with Static muscle test* (internal rotation) at end of range *(FADER-R)*. In the FADER position, the participant actively resists an external rotation force – i.e. performs static internal rotation (IR). At 90° hip flexion all portions of GMed and GMin are internal rotators [25]. This test requires the participant to activate these muscles, and therefore place further tension across their tendons, while they are in a compressed state. Again, a positive result refers to reproduction of pain at the lateral hip. As clinical features of gluteal tendinopathy include pain reproduction with elongation and compression of the involved tendons, as well as active contraction of these tendons, these two tests together may have improved diagnostic accuracy. This test is a modification of the resisted external de-rotation test, which has been reported to have 88 % sensitivity and 97.3 % specificity [26].C.*Hip FABER* – (FABER = Flexion/Abduction/External Rotation). The lateral malleolus of the test leg is placed above the patella of the opposite side, the pelvis is stabilised via the opposite anterior superior iliac spine (ASIS) and the knee is passively lowered into abduction and external rotation. This test places the anterior portions of the GMed and GMin on tensile load. A positive pain response is usually felt in the lateral hip region. Lateral hip pain with a FABER test has been shown to have a high sensitivity, specificity, positive and negative predictive value (82.9, 90, 94.4 and 72 % respectively) for differentiating the diagnosis for greater trochanteric pain syndrome from hip osteoarthritis [27].D.*Passive Hip Adduction in Side Lying (ADD)* – The participant is placed in side-lying, with the underneath hip and knee flexed 80–90°, and the uppermost leg supported by the examiner with the knee extended, in neutral rotation, and the femur in line with the trunk. The anterior superior iliac spines are aligned vertically in the frontal plane. The examiner passively moves the hip through a pure frontal plane motion into end range hip adduction with overpressure, while stablilising the pelvis with the other hand. This test places the lateral insertions of the gluteal tendons under compressive load, and a positive response is felt over the lateral hip. This is based on Ober’s test, which has been reported as having a high specificity (95 %), but a low sensitivity (41 %) and low negative predictive value (45.2 %) [27].E.*ADD with resisted isometric abduction (ADD-R)* – In the ADD test end position, the participant is asked to push the thigh up, against the resistance of the examiner’s hand at the lateral knee. This test places tensile load on the compressed tendons, with pain elicited over the lateral hip.F.*Single Leg Stance for 30 s (SLS)* – the participant stands side-on to a wall with one finger touching the wall at shoulder height for balance, then lifts the foot closest to the wall, maintaining single leg stance for up to 30 s. The participant is asked to immediately report the development of pain by pointing to the area of pain. If the region of the greater trochanter is indicated, the timer is stopped, the test ceased and recorded as positive. This time is reported, as well as the intensity of the pain. The single leg stance test has been shown to have good sensitivity and specificity (100 and 97.3 % respectively) [26] for the diagnosis of tendinopathy and bursitis in people with MRI-documented gluteal tendinopathy.

In addition to these tests, the physical screening will also ensure that the participant has ≥90°hip flexion range of movement bilaterally, knee flexion range ≥90° and full knee extension bilaterally, and that the hip quadrant test [28] is clear bilaterally. If groin pain on quadrant testing is greater than 5/10 on the Pain NRS, or the difference in pain levels between sides is greater than 2/10, the participant is excluded. Additionally, the participant must be able to flex the trunk forward with hands reaching at least to the knees with ≤2/10 back pain, and have adequate hip, knee and ankle mobility to be able to perform a squat to 60° flexion at the hips.

The participant will then be referred for MRI (if no contraindications e.g. cardiac pacemaker, metal implants etc.) and X-ray investigations at a participating radiology clinic, as a confirmed diagnosis of gluteal tendinopathy on MRI, based on a classification system from a previous study [11] will also be required for eligibility. Tendinopathy will be defined as an intratendinous increase in signal intensity on T2-weighted images (Table 2). Participants must have no contraindications to MRI (e.g. cardiac pacemaker, metal implants etc). An X-ray (AP and Lateral) is required to grade osteoarthritis severity using the Kellgren-Lawrence Scale [29]. Those with a score of >2 will be excluded from the study. To minimize unnecessary radiation exposure, if the patient has had previous appropriate X-rays within the last 6 months, they will not require a second lateral hip X-ray.

**Table 2 Tab2:** MRI Image Analysis – Classification of Pathology for definition of gluteal tendinopathy

T2 Hyperintensity around Greater Trochanter (representing oedema/fluid)	
Size	(1) Tiny (thin slit of fluid)
	(2) Small (localized, mild distension)
	(3) Medium (localized, moderate distension)
	(4) Large (localized, marked distension)
Shape	(1) Feathery
	(2) Crescentic
	(3) Round (distended bursa)
Location	(1) Subtendinous
	(2) Intratendinous*
	(3) Subfascia lata
	(4) Superficial to fascia lata
Partial thickness tear	Tendon irregular, thinned or focally discontinuous
Full thickness tear	Discontinuity and/or retraction of the torn tendon from greater trochanter

*Intratendinous high T2 signal considered as tendinopathy with a thickened tendon without any irregularity, tendon thinning, or focal tendon discontinuity

